## Abstract

**Introduction:**

Approximately 6%–10% of adults carry food allergy labels. Many such labels are unverified and may be incorrect, contributing to delays in appropriate care, significant dietary restriction, anxiety and unnecessary use of emergency medications. Oral food challenges (OFCs) are the gold standard for confirming or excluding food allergy, but the current model of clinic-based challenges often has long wait times and logistical barriers. This study aims to investigate the feasibility and safety of home-based OFCs compared with standard in-clinic challenges in adults with negative skin-prick testing.

**Methods and analysis:**

**Food C**hallenge at **HO**me or in **M**edical **P**ractice is a pilot multicentre randomised controlled trial enrolling 120 adults with reported food allergy labels and negative skin prick testing to the implicated food. Participants will be randomised 1:1 to undergo an OFC either at home or in-clinic. The study is designed to generate feasibility and preliminary safety data for home-based OFC, measured by the proportion of participants experiencing immune-mediated adverse events (AEs), compared with clinic-based OFC. Feasibility metrics (screening to recruitment ratio, protocol completion), non-immune AEs, protocol adherence and quality of life assessed using the Food Allergy Quality of Life Questionnaire-12 at baseline prior to OFC and 6 months post OFC will also be collected. Statistical analysis will include descriptive statistics, with comparisons between arms using risk differences and relative risks with 95% CIs.

**Ethics and dissemination:**

The trial has received ethics approval from the Austin Health Human Research Ethics Committee (HREC/111750/Austin-2024). Findings will be disseminated through peer-reviewed publications and scientific meetings. Data will be presented in aggregated, de-identified form.

**Trial registration number:**

NCT06916819.

STRENGTHS AND LIMITATIONS OF THIS STUDYThis is the first randomised controlled trial (RCT) evaluating the feasibility and safety of home-based food challenges compared with clinic oral food challenges (OFCs) in any population, with a particular focus on adults with negative skin prick testing.The study will provide feasibility data to inform a larger definitive trial of the efficacy of home food challenge as a ‘delabelling’ intervention.A limitation of the pilot feasibility and safety design is that the sample size will be underpowered for detecting rare severe adverse events.Results may not be generalisable beyond adult populations with negative skin-prick testing.The combination of registry and RCT data will provide a platform for future analysis of risk-predictors of positive OFC in adults.

## Introduction

 Patient-reported food allergies are a significant global health concern, with an estimated prevalence of 6%–10% among adults. The presence of a food allergy label can result in profound impacts on an individual’s quality of life, including anxiety, dietary restriction and the burden of carrying emergency medications such as epinephrine autoinjectors.^1^,^3^ Furthermore, unnecessary food avoidance may lead to nutritional deficiencies, social limitations and increased healthcare utilisation.^3 4^

Potential contributors to false food allergy labels include historical events in which a food was incorrectly identified as the trigger of symptoms and resolution of historical allergies with subsequent development of tolerance not yet recognised by the patient. A substantial proportion of patient-reported food allergies in adults are unverified and may be incorrect.^1^ Such labels are suspected to persist due to the absence of robust data to guide clinicians in challenging food allergy labels in adults, factors relating to delayed access to diagnostic food challenges or patient anxiety.

At present, there is no standard definition of a ‘low-risk’ adult patient-reported food allergy—one that is likely to be proven false on food challenge. The absence of sensitisation, as measured by negative skin prick testing (SPT) (<3 mm greater than the negative control) has been suggested to have sufficient sensitivity to ‘practically exclude’ food allergy; however, case literature exists of reactions to food challenge with negative skin testing prior.^5 6^

In this study, negative skin testing to the implicated allergen immediately prior to challenge is used to define a ‘low-risk’ patient reported food allergy appropriate for home challenge.

Despite advances in the performance of in vitro diagnostic methods such as basophil activation testing and component resolved diagnostics, a key limitation in current practice remains the challenge of timely and accurate confirmation of food allergy in vivo. The current gold standard for diagnosing food allergy is the double-blind, placebo-controlled food challenge (DBPCFC).^7^ However, DBPCFCs are resource-intensive and rarely feasible outside research settings.^8^ In clinical practice, open oral food challenges (OFCs) are widely employed to confirm or refute suspected allergies. Nevertheless, in-clinic food challenges pose significant logistical challenges, including the need for specialised facilities, trained staff and extended appointment durations.^8 9^

Even when food challenges are successfully performed in-clinic, up to 20%–40% of patients fail to reintroduce a challenge-tolerated food into their diet due to persistent anxiety or lack of confidence.^10^ This highlights a critical gap in translating negative challenge outcomes into meaningful changes in patient behaviour.

Home-based food challenges have been proposed as a potential strategy to improve access, reduce healthcare burdens and possibly enhance real-world reintroduction of foods.^711^,^13^ While guidelines and expert opinion have proposed criteria for safe home challenges, these recommendations are largely derived from paediatric populations, and there remains no prospective trial data assessing the feasibility or safety of home food challenges, particularly in adults.^11^ To date, no randomised controlled trials (RCTs) have directly compared home-based to clinic-based food challenges in any population.

The **Food C**hallenge at **HO**me or in **M**edical **P**ractice (FoodCHOMP) study aims to address this knowledge gap by evaluating the safety and feasibility of home-based food challenges in adults with low-risk food allergy labels. This pilot RCT seeks to generate critical data to inform the design of larger definitive trials and to explore whether home challenges may represent a viable and safe alternative to standard in-clinic testing for selected low-risk patients.

## Methods and analysis

### Study design

FoodCHOMP is a pilot multicentre, prospective, RCT designed to evaluate the safety and feasibility of home-based food challenges compared with standard in-clinic challenges. The trial will be conducted at two tertiary referral allergy centres in Melbourne, Australia: Austin Health and the Royal Melbourne Hospital.

All adult patients referred to the outpatient allergy services of these hospitals with a reported food allergy will undergo standard assessment including detailed clinical history and SPT as part of routine clinical practice. The requirement for endorsement of a referring clinician (eg, primary care, emergency physician) is to exclude spurious self-reported labels in the absence of a history of reaction. Patients with negative SPT to the implicated food allergen (weal size <3 mm greater than the negative control) will be assessed for trial eligibility. Blood collection for assessment of food allergen specific IgEs, where not previously available, will be collected at the time of recruitment; however, clinicians will remain blinded to these results at the time of randomisation.

Participants meeting inclusion criteria will be randomised in a 1:1 ratio to either a home-based OFC (intervention arm) or an in-clinic OFC (standard of care arm). The trial will enrol a total of 120 participants (60 per arm). The study is designed to generate feasibility and preliminary safety data to inform a larger definitive trial assessing non-inferiority of home-based food challenges.

The trial is registered with ClinicalTrials.gov (NCT06916819) and will adhere to the Consolidated Standards of Reporting Trials extension for pilot and feasibility trials.

### Eligibility criteria

Participants screened for the FoodCHOMP trial include all adults referred to outpatient allergy services with a reported food allergy label. Eligibility criteria were designed to maximise safety during food challenge procedures (Box 1). Inclusion criteria focus on individuals with negative SPT to the implicated food allergen at the time of screening and capacity to provide informed consent. Conversely, a range of exclusion criteria are applied to minimise risk, including the exclusion of specified medical conditions such as poorly controlled asthma, and use of medications that could interfere with challenge outcomes. These criteria are designed to identify a cohort considered low-risk for a severe allergic reaction and/or poor clinical outcome in the event of a severe allergic reaction (eg, uncontrolled asthma or advanced cardiac disease). Where participants have documentation of prior sensitisation to the selected food allergen (ie, previously positive skin tests or allergen specific IgE) skin testing was performed in duplicate. Patients with a reported food allergy label with a screen fail are eligible for the trial registry of the FoodCHOMP.

Box 1Inclusion and exclusion criteria
*Inclusion criteria*
Participants will be eligible for inclusion if they meet all of the following criteria:Aged 18 years or older.Referred to the outpatient allergy clinic with a reported food allergy label.Negative skin prick testing (weal <3 mm greater than the negative control) to the food implicated in their allergy label.Able and willing to provide informed consent.
*Exclusion criteria*
Participants will be excluded if any of the following criteria are present:Pregnancy.Poorly controlled asthma, defined as an Asthma Control Questionnaire-5 score >1 at the time of enrolment.History of food reactions inconsistent with IgE-mediated processes (eg, exclusively gastrointestinal symptoms, food protein-induced enterocolitis syndrome).Clear history of food-dependent exercise-induced anaphylaxis.Current use of medications that may influence the outcome of the challenge, including:Antihistamine therapy.Systemic corticosteroids at doses exceeding stress-dose thresholds (ie, >50 mg hydrocortisone four times daily or equivalent).Omalizumab or alternate biologic therapy.Any other illness or condition that, in the investigator’s judgement, would substantially increase the risk associated with participation in the study.

### Recruitment and consent

Potential participants will be identified from referrals to the outpatient allergy services at participating hospitals. All patients referred with a reported food allergy label will undergo standard clinical assessment, including detailed allergy history and SPT.

Patients who meet eligibility criteria based on negative SPT will be approached by the research team to discuss participation in the trial. Verbal and written information about the study will be provided, and written informed consent will be obtained before participation.

Those who fail to meet eligibility criteria or consent will be included in a trial registry. A waiver of consent has been obtained for the collection of routine clinical data from standard allergy assessments for patients not enrolled in the randomisation arm to be included in the registry. This data includes demographics, information on all reported food allergy labels, general allergy history, comorbidities, current medications and previous allergy testing outcomes. Data will be collected in a de-identified format.

### Randomisation

Eligible participants will be randomised in a 1:1 ratio to either the intervention arm (home-based food challenge) or the control arm (standard in-clinic food challenge). Randomisation will be performed using a permuted block design, stratified by hospital site, participant gender and evidence of prior sensitisation to the challenge food, to ensure balanced allocation across study arms.

The randomisation sequence will be generated in Stata and delivered through REDCap (Research Electronic Data Capture), hosted on secure servers at Austin Health. Allocation concealment will be ensured until the point of randomisation. Investigators and participants will not be blinded to group assignment due to the nature of the intervention.

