Exploratory outcomes include:Change in food allergy-related quality of life, assessed using the Food Allergy Quality of Life Questionnaire-12 at baseline, 1 month and 6 months postchallenge (online supplemental material 3).Degree of active consumption of the implicated food following a negative challenge result 1 month and 6 months postchallenge.Time from referral to completion of food challenge.Health economic impact of home-based compared with in-clinic food challenges.

Participants in both arms will undergo baseline, 1-month and 6-month food allergy quality of life assessment using the FAQLQ-12 and assessment of degree of consumption of the challenged food (online supplemental material 3).^14^

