### Sample size and statistical analysis

A total of 120 participants (60 per arm) will be recruited for this pilot trial. This sample size will provide estimates of safety and recruitment feasibility outcomes with a precision of <20% (total width of CIs). The chosen sample size is also considered sufficient to generate reliable estimates of safety and potential efficacy for planning a future definitive trial, as precision gains diminish beyond approximately 60 participants per group for binary outcomes.^15^

All analyses will follow the intention-to-treat principle, with supplementary per-protocol analyses conducted for sensitivity. Continuous variables will be summarised as medians with IQRs, while categorical variables will be presented as frequencies and percentages.

Binary outcomes will be presented as counts and proportions with exact 95% CIs. Comparative analyses between study arms will report absolute risk differences and relative risks, each with 95% CIs, using generalised linear models with a binomial family and identity or log link functions as appropriate.

No interim analyses are planned for this pilot study. Missing data are expected to be minimal and, where necessary, will be described in reporting.

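### The stated handling of FAQLQ-12 gives no between-arm effect with a CI, and a baseline-adjusted comparison would be more precise from the same data; for the primary outcome, using the randomisation strata is a minor supporting step.

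*Protocol article*

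**What the plan says.** All references are to the protocol article.

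- **Randomisation:** permuted blocks, "stratified by hospital site, participant gender and evidence of prior sensitisation to the challenge food". Participants and investigators know the arm once it is assigned.
- **Sample size and statistical analysis, binary outcomes:** "Comparative analyses between study arms will report absolute risk differences and relative risks, each with 95% CIs", from binomial models with an identity or log link. No stratum or covariate is named, and the models are not described as unadjusted.
- **Same section, continuous data:** "Continuous variables will be summarised as medians with IQRs". Nothing further is given for continuous outcomes.
- **Outcomes, Box 2 (exploratory):** "Change in food allergy-related quality of life, assessed using the Food Allergy Quality of Life Questionnaire-12 at baseline, 1 month and 6 months postchallenge".
- **Abstract:** baseline FAQLQ-12 is timed before the food challenge. Its position relative to randomisation is not given.
- **Study design:** "The study is designed to generate feasibility and preliminary safety data to inform a larger definitive trial assessing non-inferiority".

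**The concern.** FAQLQ-12 is collected three times per participant. Read together, the outcome definition and the analysis section yield medians and IQRs of a change score in each arm. That describes each arm, but it does not give an estimated difference between home and clinic challenge with its uncertainty, which is what a pilot can usefully hand on. If the arms are later contrasted on mean change, the contrast is unbiased but less precise than one that adjusts follow-up score for baseline.

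A patient-reported baseline also needs to be free of knowledge of the arm. In an open trial, a questionnaire timed only as before the challenge could be completed after the participant has learned whether the challenge will be at home. That would weaken both a change score and an adjusted analysis.

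For the primary outcome the issue is smaller. Where stratification factors predict the outcome, stratified allocation reduces the true variability of the risk difference. A standard error that ignores the strata does not show this and comes out slightly too large.

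**Working it through.** **1. The plan's own figure.** "A total of 120 participants (60 per arm) will be recruited for this pilot trial". The stated precision is a total CI width below 20 percentage points, and "Binary outcomes will be presented as counts and proportions with exact 95% CIs". The exact (Clopper-Pearson) 95% width at n = 120 is greatest at 60/120, where the limits are 0.407 and 0.593, a width of 18.5 points. The figure is therefore reproduced for the whole sample. With 60 in one arm it holds up to 9/60 (19.5 points) but not at 10/60 (20.2 points). The target concerns single proportions, so nothing below alters it.

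**2. FAQLQ-12: change score against ANCOVA.** The article gives no correlation between baseline and follow-up, so ρ is assumed over a range. With equal variance σ² at both times:

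- change-score variance per participant: 2(1 − ρ)σ²
- ANCOVA variance per participant: (1 − ρ²)σ²
- ratio: 2(1 − ρ)/(1 − ρ²) = 2/(1 + ρ)
- ANCOVA sample matching 120 on change scores: 120(1 + ρ)/2

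| ρ (assumed) | Change | ANCOVA | Ratio | Matching n |
|---|---|---|---|---|
| 0.4 | 1.20 | 0.84 | 1.43 | 84 |
| 0.5 | 1.00 | 0.75 | 1.33 | 90 |
| 0.7 | 0.60 | 0.51 | 1.18 | 102 |
| 0.9 | 0.20 | 0.19 | 1.05 | 114 |

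At ρ = 0.5 the standard error falls to √0.75 = 0.87 of the change-score value; at 0.9 it falls only to √0.95 = 0.975.

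**3. Primary outcome: use of the strata.** No event rates are given, so all rates here are assumed. Let s be the share previously sensitised, a and b the risks with and without sensitisation, and p = sa + (1 − s)b.

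- variance explained: R² = s(1 − s)(a − b)²/[p(1 − p)]
- unadjusted width of the risk-difference CI: 2 × 1.96 × √[2p(1 − p)/60]
- adjusted width: the same × √(1 − R²)

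| s | b | a | p | R² | Width, points | Narrowing |
|---|---|---|---|---|---|---|
| 0.1 | 5% | 10% | 5.5% | 0.004 | 16.32 → 16.28 | 0.2% |
| 0.2 | 3% | 15% | 5.4% | 0.045 | 16.2 → 15.8 | 2.3% |
| 0.3 | 5% | 30% | 12.5% | 0.120 | 23.7 → 22.2 | 6.2% |

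The first and last rows are the extremes of the grid examined (s from 0.1 to 0.5).

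**4. Simulation check.** Eight strata (two levels per factor, assumed), blocks of 4 (assumed), 3000 trials per scenario, unadjusted risk difference against a covariate-adjusted linear model with robust standard errors:

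- True SD of the estimate, unadjusted and adjusted: 0.0332 and 0.0333 at about 3.6% events; 0.0569 and 0.0566 at about 12.5%. Stratified allocation has already supplied the balance.
- Mean reported standard error: 0.0328 → 0.0324 in the low-rate case; 0.0594 → 0.0561 in the strongest case.
- Unadjusted coverage: 94.8% to 95.9%.
- At about 3.6% events, roughly 59% of strata contain no event, and about 20% of trials have an arm with none.

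**The case against.** The strongest reply is that a journal article condenses the protocol, and that covariate lists and secondary models are commonly left to an analysis plan, which is not shown here. For the primary outcome this largely stands: silence about strata does not show that they will be ignored. It has less force for FAQLQ-12, where the article fixes both a change outcome and a descriptive summary. Even there, no between-arm FAQLQ-12 analysis is stated, so the ratios in the working compare ANCOVA with the natural contrast of mean changes, not with a method the article has committed to.

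Several stronger readings are tempting and are not supported:

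- *That baseline FAQLQ-12 goes unused.* It is the reference for the change outcome. The issue is efficiency.
- *That the primary comparison is invalid, or materially imprecise, without the strata.* Coverage holds, and the effect on the reported CI is small.
- *That adjusting the primary model is free of cost.* With few events, an identity- or log-link binomial model with three covariates may fail to converge or have terms that cannot be estimated. A simple primary model is defensible.
- *That prior sensitisation was made a stratum because it predicts reaction.* The stated reason is balance between arms. Prediction is plausible, since previously sensitised participants have skin tests in duplicate, but it remains an inference.
- *That the baseline questionnaire follows allocation.* The article leaves the order open and does not say so.
- *That the definitive trial will be sized on FAQLQ-12.* The article does not say this.

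**Conclusion.** This is a free improvement, not an error that threatens validity. Its main part is FAQLQ-12: the article states no between-arm effect with a CI, and ANCOVA would give a more precise one from data already being collected. The gain rests on the unknown correlation. A change score carries 1.33 times the variance at 0.5 but only 1.05 times at 0.9, assuming similar variances at baseline and follow-up. The outcome is exploratory, which limits the consequence.

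For the primary outcome, if the strata predict reaction, the unadjusted CI is slightly conservative. Adjustment would narrow it by about 0.2% to 6% under the assumed rates, with the estimate's true variability essentially unchanged. That justifies at most a supporting analysis. Neither the 120 participants nor the precision target changes.

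**What to change.** - **FAQLQ-12.** State that scores at 1 and 6 months will be compared by ANCOVA, or by a mixed model across both visits, with baseline score and the stratification factors as covariates. Report adjusted mean differences with 95% CIs, and keep the medians and IQRs beside them.
- **Baseline timing.** State that the baseline questionnaire is completed before allocation is revealed.
- **Primary outcome.** State whether the comparisons use the strata. As a supporting analysis, add a Mantel-Haenszel risk difference over the randomisation strata with a stratified score CI. This tolerates strata without events, which covariates in an identity-link model may not. The planned simple comparison can remain the main result.

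The analysis changes cost a few sentences and need no new data. The timing point needs one procedural sentence and, if sites currently collect the questionnaire after randomisation, a change in the order of steps.

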### Treatment arms

#### Home-based food challenge (Intervention arm)

Participants randomised to the intervention arm will undertake a home-based OFC following a structured protocol. An initial supervised dose of the implicated food will be administered in-clinic with a 60-minute observation period to assess for immediate reactions. If no reaction occurs, participants will proceed to continue the challenge at home.

The home challenge protocol involves graded daily dosing over 5 days, beginning with a small initial amount and increasing to a full serving by Day 5, provided no adverse reactions occur. The dosing schedule for the home challenge is detailed in figure 1 and doses are drawn from the Food Allergy Challenge Doses table (online supplemental material 1). Participants will receive written patient instructions outlining the protocol, symptom monitoring and emergency management (online supplemental material 2). Participants are advised to abstain from exercise for 2 hours following each dose. Participants are otherwise encouraged to continue their typical occupation during the challenge period with restriction.

